**Fig. 2 Fig2:**
[figure not shown]
Standard Protocol Items: Recommendations for Interventional Trials (SPIRIT) Figure

### Outcomes

The primary outcome for this study is 28-day mortality rate among preterm infants. For this primary analysis, the denominator will include:All live births weighing greater than 1000 g and less than 2500 gAll live births weighing between 2501 g and 3000 g with a documented GA of less than 37 weeksAll fresh stillbirths weighing greater than 1000 g and less than 2500 gAll fresh stillbirths weighing between 2501 g and 3000 g with a documented GA of less than 37 weeks

This outcome will be measured by comparing mortality rates of preterm infants at 28 days after delivery across the intervention and control arms to determine the effect of the package of facility-level interventions. The upper limit of 3000 g (which is coupled to a documented GA of less than 37 weeks) was agreed upon based on INTERGROWTH-21st standards. At this weight, we assume that we will capture 90% and 97% of < 34-week infants and 60% and 70% of < 37-week infants, for female and male children, respectively [22]. The lower limit of inclusion for the primary analysis was set at 1000 g to align with the *International Classification of Diseases 10th revision* (ICD 10) definition of late fetal death (i.e., birthweight of > 1000 g or > 28 weeks’ gestation) [6]. However, data on infants with signs of life born weighing < 1000 g will be followed for secondary data analyses, including outcomes at 28 days of life. Selected secondary outcomes are listed in Table 2.We include additional information as to how they will be measured and how often during the study duration.

**Table 2 Tab2:** Select secondary outcomes

Secondary outcome	How variable will be measured	Time frame
Data quality of key indicators in facility-based registers (includes GA, facility discharge status, preterm birth incidence)	GA-birthweight concurrence, DQAs and mSCC data review or QI indicators	Baseline through study completion, an average of 18 months; at least quarterly
Pre-discharge mortality among all infants > 1000 g	Clinical record review at facility	Baseline and through study completion, an average of 18 months
Facility-based maternal mortality	Clinical record review at facility	Baseline and through study completion, an average of 18 months
Perinatal mortality (fresh stillbirths and deaths within 7 days) among eligible preterm infants (includes pre-discharge mortality)	Parental report at 28 days and clinical record review at facility	Baseline and through study completion, an average of 18 months
Mortality among preterm infants and those born alive between 500 g and 999 g at birth (include pre-discharge mortality and 28-day mortality)	Parental report at 28 days and clinical record review at facility at time of first contact	Baseline and through study completion, an average of 18 months
Average number of EBPs or Ministry of Health management guidelines demonstrated in simulated case videos and live birth observations	Measured in PRONTO simulation videos, observed live births and/or mSCC. To be complemented by pre-post knowledge tests and facility assessments	Baseline and through study completion, an average of 18 months. PRONTO administered at pre-determined time points
Knowledge improvement of EBPs	PRONTO pre-post knowledge test scores	PRONTO administered at pre-determined time points
Proportion of eligible cases receiving EBPs reported by QI teams (QI indicators include Kangaroo Care, antenatal corticosteroid provision, and breastfeeding)	QI indicators reported at learning sessions	Baseline and through study completion, an average of 18 months; QI learning sessions held every 3–6 months
Facility readiness to handle delivery and newborn complications	Measured by a facility assessment tool	Bi-annually over the study period
Understanding of contextual factors influence implementation of strengthening maternal and newborn care interventions	Process evaluation that incorporates document review, surveys and qualitative interviews and focus groups	To be conducted mid-study
Prevalence of preterm birth phenotypes in the study sites	Retrospective and/or prospective chart review	Baseline and through study completion; at least annually in select sites

*GA* gestational age, *DQA* data quality assessment, *EBP* evidence-based practice, *mSCC* Modified Safe Childbirth Checklist, *QI* quality improvement

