**Methods/design:**

This is a pair-matched, cluster randomized controlled trial across 20 facilities in Eastern Uganda and Western Kenya. The intervention facilities receive four components: (1) strengthening of routine data collection and data use activities; (2) implementation of the WHO Safe Childbirth Checklist modified for preterm birth; (3) PRONTO simulation training and mentoring to strengthen intrapartum and immediate newborn care; and (4) support of quality improvement teams. The control facilities receive both data strengthening and introduction of the modified checklist. The primary outcome for this study is 28-day mortality rate among preterm infants. The denominator will include all live births and fresh stillbirths weighing greater than 1000 g and less than 2500 g; all live births and fresh stillbirths weighing between 2501 and 3000 g with a documented gestational age less than 37 weeks.

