### Study population

In all facilities, women accessing delivery care services who are admitted for labor will be eligible for this study. Anonymized data on all deliveries will be extracted from maternity registers. For follow-up, mothers of newborns who are discharged alive and born less than 2500 g or between 2501 g and 3000 g while also being identified as less than 37 weeks by recorded GA in the maternity register are being asked to participate in this study and approached for consent for follow-up for 28-day outcome. These inclusion parameters were selected based on baseline data showing a poor correlation between birthweight and reported GA in the maternity register. Women or newborns from enrolled sites who are referred to one of the three referral facilities will remain in the study. Their outcomes will be allocated to the facility to which the woman first presented.

Healthcare workers providing labor and delivery and immediate newborn care services at referral, control, and intervention facilities will participate in DS initial and refresher workshops, DQAs, as well as initial instruction and minimal refreshers or reorientation on use of the mSCC. Intervention sites will have ongoing support for mSCC utilization, in addition to the other reinforcing intervention components, PRONTO and QI. Healthcare providers in intervention facilities who provide consent for PRONTO simulation trainings will also be enrolled as study participants to ascertain changes in knowledge and practices. Facility staff in the intervention facilities will be organized into QI teams to develop and implement QI programs.

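### The weight bands skip infants recorded at exactly 2500 g with GA below 37 weeks, and the Discussion's restatement differs from Methods at 2500 g and 3000 g

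*Protocol article*

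**What the plan says.** The protocol article states the weight limits in five places.

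- **Abstract (Methods/design):** the limits, for live-born infants and fresh stillbirths alike, read "weighing greater than 1000 g and less than 2500 g; all live births and fresh stillbirths weighing between 2501 and 3000 g", the second band requiring documented GA below 37 weeks.
- **Outcomes:** the same two bands, for live births ("live births weighing between 2501 g and 3000 g with a documented GA of less than 37" weeks) and for stillbirths ("fresh stillbirths weighing between 2501 g and 3000 g with a documented GA of less than 37 weeks"). The lower limit is justified by the ICD-10 definition of late fetal death, given as "birthweight of > 1000 g or > 28 weeks". Infants with signs of life below 1000 g are kept for secondary analyses.
- **Study population:** mothers are approached for follow-up consent if the infant left the facility alive and meets this rule: "born less than 2500 g or between 2501 g and 3000 g while also being identified as less than 37 weeks by recorded GA". There is no lower weight limit.
- **Table 2:** pre-discharge mortality covers all infants above 1000 g. Another row covers preterm infants and "those born alive between 500 g and 999 g at birth".
- **Discussion (Challenges and opportunities):** the denominator is above 1000 g and below 2500 g, or GA below 37 weeks with weight below 3000 g.

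**The concern.** The first band stops short of 2500 g and the second starts at 2501 g, so one weight is left out. It is a round weight, and birthweights come from routine registers completed by facility staff, where round values may be common. Whether a preterm infant counts in the primary outcome could then turn on how a weight was written down.

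The same gap in the consent rule matters more than it would in an analysis definition alone. Consent is taken before discharge or referral. If the rule is applied as printed, mothers of these infants are not approached, and what happens after discharge cannot be recovered later.

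The Discussion's wording closes the gap at 2500 g but drops exactly 3000 g, which Outcomes includes. A programmer working from this article could build different denominators in good faith.

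**Working it through.** **Step 1. The rules applied literally.** I read 'between' as including both ends. Each rule is tested at the boundary weights.

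| Recorded weight, documented GA | Primary (Abstract, Outcomes) | Follow-up (Study population) | Discussion wording | Pre-discharge mortality, > 1000 g | Low-weight groups (< 1000 g; 500–999 g) |
|---|---|---|---|---|---|
| 999 g, 35 wk | out | in | see note | out | in |
| 1000 g, 35 wk | out | in | see note | out | out |
| 1001 g, 35 wk | in | in | in | in | out |
| 2499 g, 35 wk | in | in | in | in | out |
| 2500 g, 35 wk | **out** | **out** | **in** | in | out |
| 2501 g, 35 wk | in | in | in | in | out |
| 3000 g, 35 wk | **in** | **in** | **out** | in | out |
| 2499 g, 38 wk | in | in | in | in | out |
| 2500 g, 38 wk | out | out | out | in | out |

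Note: in the Discussion, these two infants are in if the GA limb has no lower weight limit, and out if the 1000 g limit carries over to it.

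So 2500 g with GA below 37 weeks is an isolated hole in the primary denominator and in follow-up, and the Discussion disagrees with Outcomes at 2500 g and at 3000 g. An infant at 1000 g is followed but lies in none of the weight bands of Outcomes and Table 2.

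**Step 2. The plan's own accrual figure.** Inputs from Sample size and power calculations: 46,000 deliveries, 12% preterm, 25% lost to follow-up, 20 facilities.

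- 46,000 × 0.12 = 5,520 (stated: about 5,500)
- 5,520 × 0.75 = 4,140
- 4,140 / 20 = 207 per facility (stated: at least 200)

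The figure reproduces.

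**Step 3. How many infants sit at 2500 g with GA below 37 weeks.** The documents do not say. A simulation of 2,000,000 births assumed 12.5% preterm, weight linear in GA with SD 400 g, and error in documented GA with SD 2 weeks. The last column applies the share to 4,140 as a stand-in for the denominator.

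| Assumed recording | Share of denominator | Of 4,140 |
|---|---|---|
| To 10 g | 0.7% | about 29 |
| Half rounded to 100 g | 4% | about 166 |
| All rounded to 100 g | 7.5% | about 311 |

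A crude check: if infants were spread evenly over the 2,000 g from 1000 g to 3000 g, the interval recorded as 2500 g would hold 10/2,000 = 0.5% or 100/2,000 = 5%, the same order. Infants at exactly 1000 g come to 0.01% to 0.16% in the simulation.

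**Step 4. Power.** Standard formula for clusters per arm, two-sided 5% (sidedness assumed), 80% power, p0 = 0.25, coefficient of variation k = 0.2, p1 = p0(1 − reduction), m infants per facility:

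c = 1 + (1.96 + 0.84)² × [p0(1 − p0)/m + p1(1 − p1)/m + k²(p0² + p1²)] / (p0 − p1)²

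Setting c = 10 and solving for the reduction:

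- m = 207: 27.5%
- 5% fewer (207 infants; m = 196.6): 27.7%
- 10% fewer (414 infants; m = 186.3): 28.0%

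This unmatched formula does not return the stated 25% exactly; pair-matching or another variance form may explain that. Only the change matters here, and it is at most half a percentage point.

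**The case against.** **It is only a boundary slip, and the Discussion shows the intent.** It is most naturally a slip, but it stands in the Abstract, in Outcomes and in the consent rule. The Discussion cannot settle it alone, because it brings its own discrepancy at 3000 g. A second band starting at 2501 g could also mean that the first was meant to include 2500 g at any GA. In the same simulation, infants recorded at 2500 g at any GA come to 1.8%, 10% and 19%. Those figures do not measure the gap on the Discussion's reading, under which infants with GA of 37 weeks or more, or undocumented, stay out.

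**A reader might infer bias between arms.** If one arm kept in a further 5% or 8% of infants with 5% mortality (assumed), a 25% rate would become (0.25 + 0.05 × 0.05)/1.05 = 24.0% or (0.25 + 0.08 × 0.05)/1.08 = 23.5%. The documents do not support this. The same bands apply to both arms. Both receive data strengthening, which includes birthweight training and scale-calibration checks, and nothing suggests that rounding differs. An 8% difference also exceeds the whole simulated range (7.5 − 0.7 = 6.8 points), and 5% exceeds the step from no rounding to half rounded (4 − 0.7 = 3.3 points).

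**A reader might infer that these infants' outcomes are lost altogether.** Data on all deliveries are extracted from registers, so fresh stillbirths and pre-discharge deaths at 2500 g are recorded, and Table 2 counts pre-discharge mortality for them. Only post-discharge outcomes are at risk. The article also does not show how the eligibility filter works in practice.

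**A reader might infer that infants at 1000 g are dropped entirely.** They are eligible for follow-up, the Discussion's GA limb read literally includes them if GA is below 37 weeks, and the preterm row of Table 2 might cover them. What stands is the gap in the stated weight bands, with negligible numbers.

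**Conclusion.** Wrong as written. The Abstract, Outcomes and Study population leave out infants recorded at exactly 2500 g with documented GA below 37 weeks, both from the primary denominator and from consent to 28-day follow-up. The Discussion contradicts Outcomes at 2500 g and at 3000 g. Exactly 1000 g is in neither the primary band nor the low-weight bands, though such infants are followed.

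That the gap exists is certain from the text. Its size is not: 0.7% to 7.5% of the denominator rests on an assumed birthweight model and assumed rounding, with no register data behind it. Loss of power is small and no bias between arms is shown. The point deserves correction because it concerns the primary outcome, decides whom to approach for consent, and is cheap to put right.

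**What to change.** Use one contiguous definition in the Abstract, Study population, Outcomes, Table 2 and the Discussion:

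- **Primary, any GA:** above 1000 g and below 2500 g.
- **Primary, documented GA below 37 weeks:** 2500 g to 3000 g, both ends included.
- **Secondary low-weight band:** 500 g to 1000 g, both ends included.

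The gap at 1000 g is closed in the secondary band, so that the primary limit of above 1000 g, which the article justifies, stays as it is. The investigators should confirm that infants at 2500 g are meant to count only with GA below 37 weeks, as the Discussion implies.

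Apply the same limits at 2500 g and 3000 g to the consent and follow-up list. For births at 2500 g before the change, use register and pre-discharge data. Report a sensitivity analysis on the old limits, because ascertainment at 2500 g will differ by calendar time.

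The cost is a small amendment, a changed eligibility filter and a few extra follow-up calls, roughly in proportion to the 0.7% to 7.5% above. Enrolment was still open when the article was written, so earlier correction saves more outcomes.

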### Data collection/quality control

For the primary outcome, existing facility-based registers will be used as primary data sources. Data entry into registries is conducted by facility care providers, as part of existing routine data collection. Information in these registries will then be extracted by study personnel. Study staff will visit each facility at least once per month to collect routine facility data from register reviews. All data will be uploaded via Open Data Kit via tablet or laptop.

For preterm babies discharged alive from hospital, mothers will be consented to be followed up by phone at 28 days following delivery. Consent of eligible mothers and their newborns will take place prior to discharge or referral. Contact information will be derived from consent forms, and from the mSCC as needed. Outcomes will be determined by targeted follow-up of study participants via phone call. Where phone calls are insufficient to trace mothers, the Kenya team will engage with community health volunteers and Uganda will employ community outreach nurses to seek out mothers.

#### Data strengthening

Study personnel in each country will collect data from maternity registers on a monthly basis. In addition to reviewing the quality of records, they will also generate summary reports for data sharing among the research team and facility leads.

Routine indicators and process indicators for QI cycles will be collected and displayed on a Data Dashboard accessible to study staff, intervention and referral health facility staff, and county health authorities. While these Data Dashboard displays will be customized to different audiences, all of the data included will be aggregate, and no individual data will be displayed.

#### Modified Safe Childbirth Checklist (mSCC)

The mSCC will be distributed to facilities and fixed into the patient charts in readiness for use by the healthcare providers. Staff will be adequately trained on the use of the checklist and regular reinforcement conducted as scheduled at intervention sites. Study staff will review all maternity charts for newborns who meet our eligibility criteria. Each month, they will abstract key data from eligible admissions from the mSCC in order to compile coverage indicators for key interventions and EBPs. Uptake and completeness of the mSCC will also be determined.

#### PRONTO simulation-based training

To measure changes in knowledge through training and mentoring, we will conduct evaluations in the form of pre- and post-knowledge tests of PRONTO-trained midwives, nurses, and physicians before and after each training session and periodically during mentoring visits. These evaluations will be adapted to the local context based on previously developed knowledge assessment tools used by PRONTO. To evaluate the impact of PRONTO’s on-site simulation training program, we will collect video-recordings of simulated birth scenarios and debriefs conducted in participating hospitals led by PRONTO-trained mentors/trainers. These videos will be coded using Studiocode™ software to create scores based on how often EBPs are practiced in simulation and if this changes over time.

#### Quality improvement (QI) cycles

We will track process indicators of these QI cycles, such as number of projects started, number of goals reached, and amount of change detected by the QI team in studying their implementation. We will implement a QI documentation journal for the sites. QI teams will also track key EBPs, such as Kangaroo Care uptake, and track their progress against it.

### Data management

Data from registries will be collected using a secure database via the Open Data Kit data entry platform and hosted on a secure server. Data will be reviewed for accuracy and completeness by a data manager before entry, and the data entry system will include automated range and logic checks to identify any data entry mistakes before they are saved. All devices used for data entry (laptops or tablets) will be encrypted and password protected.

The research team and stakeholders will have access to aggregate data across facilities through the Data Dashboard. For example, each facility will have access to their own data including 28-day outcome, but stratified data by control and intervention data will not be shared. Moreover, only the study biostatistician and core team will have access to the unblinded dataset prior to study completion.

### Sample size and power calculations

Our primary analysis will combine data across our selected facilities in Kenya and Uganda. Since we will exclude the referral hospitals from our primary analysis, the project takes place in 20 facilities with an expected volume of 46,000 deliveries over 24 months. In an initial calculation, prior to baseline data collection, we assumed an average preterm birth rate of 12% and expected to see about 5500 preterm deliveries within this period. We assumed a 25% loss-to-follow-up rate for eligible cases. This yields at least 200 projected preterm deliveries per facility with known 28-day mortality outcome.

Detectable effect sizes were estimated by standard *t* test procedures adjusted to account for the design effect due to clustering of outcomes within facilities to attain 80% power while maintaining type I error at 5%. At a 25% 2-year cumulative incidence of 28-day mortality across both countries in the absence of the intervention, this would allow us to detect a 25% reduction in cumulative incidence if the between-cluster outcome coefficient of variation is 0.2 or below. If this coefficient increases to 0.3, we would be powered to detect a 30% reduction. If it increases to 0.4, we would be powered to detect a 40% reduction.

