### Setting and site selection

The study regions of Migori County, Kenya and Busoga Region, Uganda were selected based on in-country stakeholder input. Prematurity burden and presence of synergistic parallel maternal/newborn research or implementation studies were considered. Health facilities were asked to participate in this study by in-country partners. Formal approval from facility leadership was obtained before any activities commenced. Given that facilities were not selected from a target population of hospitals, the intervention effects should be interpreted as impact evaluation of the intervention package implemented at the said facilities. A complete list of all facilities can be found at the clinical trial registration (ClinicalTrials.gov, ID: NCT03112018).

The Busoga Region of Eastern Uganda contains approximately three million people, or 10% of Uganda’s population, with over 80% of residents living on less than US$1 per day [21]. The estimated preterm birth rate for Uganda is 13.57% and the neonatal mortality rate is 21 per 1000 live births [3, 4]. Our selected six health facilities include approximately 22,000 deliveries per year, with 9000 deliveries from the four hospitals pair-matched in this study. Migori County, located in southwestern Kenya, has a population of approximately 917,170, wherein 43% of the population lives below the poverty line [21]. The estimated preterm birth rate for Kenya is 12.30% and the neonatal mortality rate is 23 per 1000 live births [3, 4]. Our 17 selected Migori County health facilities include approximately 10,000 deliveries per year, with 7500 deliveries at pair-matched sites.

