### Intervention roll-out

The approach for roll-out of the intervention package will be as follows:*Baseline*: Across all selected facilities, preliminary DS with initial introduction of the mSCC will allow us to conduct a baseline survey to measure incidence of preterm births and preterm mortality in all facilities (at least 2 months). Baseline data will also be collected on key variables that are predictive/correlated with the primary outcome of mortality rate among preterm infants, including but not limited to number of deliveries, number of low birthweight babies, number of neonatal deaths, number of stillbirths, presence of a newborn corner, personnel capacity for intrapartum/postnatal care, etc.*Step 1*: Facilities will be pair-matched using key factors correlated with outcomes. Specifically, sites will be pair-matched based on variables collected during baseline that are predictive or correlated with the primary outcome of mortality rate among preterm neonates (i.e., delivery volume, number, and type of providers, facility-based neonatal mortality rate).*Step 2*: Within each matched pair, one facility will be randomized to the intervention arm and the other will be randomized to the control arm. Intervention facilities will receive PRONTO and QI interventions in addition to DS and mSCC. Randomization and allocation will be done using a computerized random number generator by the statistical team with no contact or direct interest in any specific facilities. As this is a cluster trial, there will be no blinding or allocation concealment.*Step 3*: Upon accruing sample size, the control arm facilities will be assigned to the full intervention, adding PRONTO training and QI cycles.

Figure 2 depicts the schedule of enrollment, interventions, and assessments to be conducted.

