## Trial status

This trial has completed planning and began enrollment in October 2016. Study enrollment is ongoing with expected completion by October 2018.

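### The sample size rests on 46,000 deliveries in 24 months, but the protocol's own volumes for the same 20 facilities give 33,000, so the projected infants per facility fall from about 207 to about 149 on average

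*Protocol article*

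**What the plan says.** The protocol article gives the delivery volume of the randomised facilities in two places.

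- **Sample size and power calculations.** The calculation opens with "Since we will exclude the referral hospitals from our primary analysis" and continues that "the project takes place in 20 facilities with an expected volume of 46,000 deliveries over 24 months". It then assumes a 12% preterm birth rate, giving about 5500 preterm deliveries, and 25% loss to follow-up. It concludes: "This yields at least 200 projected preterm deliveries per facility with known 28-day mortality outcome". The detectable reductions follow: 25%, 30% and 40% at between-cluster coefficients of variation of 0.2, 0.3 and 0.4, with 80% power, 5% type I error and 25% control mortality.
- **Setting and site selection.** For Uganda: "Our selected six health facilities include approximately 22,000 deliveries per year", "with 9000 deliveries from the four hospitals pair-matched in this study". For Kenya, 17 facilities have about 10,000 deliveries a year, "with 7500 deliveries at pair-matched sites".

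The Trial design section gives four randomised facilities in Uganda and 16 in Kenya. Two other statements depend on the sample size. Step 3 of Intervention roll-out reads: "Upon accruing sample size, the control arm facilities will be assigned to the full intervention". The Trial status section gives an enrolment start of October 2016 and says: "Study enrollment is ongoing with expected completion by October 2018".

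**The concern.** Both volumes describe the same 20 facilities with the referral hospitals left out, yet they differ by 13,000 deliveries over two years. The larger one is the only basis given for the number of infants, and through it for the detectable effects.

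The per-facility figure is also worded as a floor, although it comes from dividing a total by 20. By the site description, four Ugandan hospitals carry 9000 of 16,500 deliveries (55%) and 16 Kenyan sites share the rest, so a typical cluster is far from the average.

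At stake are the precision the trial can claim and the meaning of the sample size whose accrual ends the controlled comparison.

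**Working it through.** **Inputs.** From the sample size section: 46,000 deliveries in 24 months, 12% preterm, 25% loss, 20 facilities, control mortality 25%. From Setting and site selection: 9000 and 7500 deliveries a year at pair-matched sites; 22,000 and 10,000 a year at all sites. From Trial design: 4 Ugandan and 16 Kenyan randomised facilities.

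**1. The protocol's own chain reproduces.**
- 46,000 × 0.12 = 5520 preterm deliveries (stated: about 5500)
- 5520 × 0.75 = 4140 with a known outcome
- 4140 / 20 = 207 per facility (stated: at least 200)

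The arithmetic after the first input is sound, but 207 is a mean across facilities.

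**2. The first input does not reproduce.**
- (9000 + 7500) × 2 = 33,000
- 46,000 / 33,000 = 1.39, so the stated volume is 39% higher
- All sites including referral hospitals: (22,000 + 10,000) × 2 = 64,000, which does not give 46,000 either

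**3. The chain from 33,000.**

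| Quantity | Formula | Result | Stated |
|---|---|---|---|
| Preterm deliveries | 33,000 × 0.12 | 3960 | about 5500 |
| Known outcome | 3960 × 0.75 | 2970 | 4140 (implied) |
| Average per facility | 2970 / 20 | 148.5 | at least 200 |
| Average Kenyan site | 7500 × 2 × 0.12 × 0.75 / 16 | 84.4 | – |
| Average Ugandan hospital | 9000 × 2 × 0.12 × 0.75 / 4 | 405 | – |

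**4. Sensitivity of the per-facility figure, starting from 33,000.**
- No loss at all: 3960 / 20 = 198 on average; 15,000 × 0.12 / 16 = 112.5 at the average Kenyan site
- Country preterm rates from the site description (12.30% and 13.57%): (15,000 × 0.1230 + 18,000 × 0.1357) × 0.75 / 20 = 161 on average; 86 at the average Kenyan site
- Eligible fraction needed for an average of 200: 200 × 20 / 0.75 / 33,000 = 16.2%

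**5. Effect on power.** Simulation with beta-distributed facility risks and binomial deaths, 20,000 replicates. The test is a two-sided unpaired t test on facility proportions at 5% (the article does not state sidedness). I assumed 2 Ugandan and 8 Kenyan pairs and no gain from matching or covariates.

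| CV / reduction | 207 in every facility | 148 in every facility | 405 × 2 and 84 × 8 per arm |
|---|---|---|---|
| 0.2 / 25% | 71% | 66% | 59% |
| 0.3 / 30% | 62% | 59% | 55% |
| 0.4 / 40% | 69% | 67% | 65% |

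A hand check for the first row uses variance per pair of facilities = [p0(1−p0) + p1(1−p1)]/m + k²(p0² + p1²), with p0 = 0.25 and p1 = 0.1875.
- At m = 207: 0.3398/207 + 0.04 × 0.0977 = 0.00555. The SE with 10 per arm is √(0.00555/10) = 0.0236, the ratio is 0.0625/0.0236 = 2.65, and power on 18 df is 71%.
- With unequal sizes, m is replaced by the harmonic mean 20 / (4/405 + 16/84.4) = 100. The SE is 0.0270, the ratio 2.31 and power 59%.

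**6. Time to reach the implied total.** At 16,500 deliveries a year, known outcomes accrue at 16,500 × 0.12 × 0.75 = 1485 a year. The implied 4140 would take 4140 / 1485 = 2.8 years (33.5 months). October 2016 to October 2018 is 24 months.

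**The case against.** **It was a provisional calculation.** The section labels the preterm projection an initial one, made before baseline data. That may explain an outdated figure. But the label introduces the 12% and the 5500; the 46,000 stands as a current expectation in the sentence before, and no update is given.

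**Referred cases remain in the analysis.** The article retains women and newborns referred from the 20 facilities. Closing the gap this way would need 23,000 − 16,500 = 6500 extra deliveries a year. That is 42% of the 15,500 (32,000 − 16,500) at the referral hospitals. Nothing in the article says this, and it ties the 46,000 to the 20 facilities.

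**The eligible fraction may exceed 12%.** This one has force. Eligibility includes every live birth or fresh stillbirth between 1000 g and 2500 g whatever the gestational age, and the article gives no eligible fraction. A value near 16.2% would restore an average of 200. It would not reconcile the two delivery volumes, and the average Kenyan site would still be at about 15,000 × 0.162 × 0.75 / 16 = 114.

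**The wording about 200 may only be 207 rounded down.** That is a fair reading of intent. As written, it still describes a minimum per facility that the calculation does not provide.

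**Most of the shortfall from 80% power has another source.** This stands. With 207 infants in every facility, the simulation already gives only 71/62/69%. A reader might infer that the volume error explains the whole gap; it does not. The formula behind the stated effects is not shown, and gains from matching or from the planned covariate-adjusted estimator could have been assumed.

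**Step 3 is not shown to be unattainable.** A reader might infer that the control crossover can never be triggered by its own rule, for instance because a Kenyan site would take years to reach 200. The article attaches no number to Step 3 and does not make 200 per site a condition, so that inference is unsupported.

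**Conclusion.** The point holds as a contradiction between two current statements in the article. The volume behind the sample size is 39% above what the site description gives for the same facilities. On the protocol's own rates, the expected total with known outcome is 2970 rather than 4140 (28% lower). The average Kenyan site, representing 16 of the 20 clusters, has about 84 infants, under half of the stated 200.

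The cost in power is real but moderate, because variation between facilities dominates. Lower volume and unequal sizes together take about 12, 7 and 4 points from the three stated scenarios; lower volume alone takes about 5, 3 and 2. These losses rest on the assumed pair composition, equal sizes within each country, equal weight per facility, and no benefit from matching or covariates.

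For Step 3, the finding is that the sample size it refers to is not stated. The only total that the calculation implies, about 4140, would take about 2.8 years at the site-description volumes, beyond the stated 24 months. The documents do not support saying that the crossover rule itself must fail.

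**What to change.** 1. Reconcile the volumes in Setting and site selection with those in Sample size and power calculations, and say which are current.
2. Replace the 46,000, the 5500 and the minimum of 200 with figures derived from the reconciled volumes. Give the expected number per facility separately for Kenya and Uganda, and call an average an average.
3. Restate the detectable effects using those unequal cluster sizes, and name any gain assumed from matching or covariate adjustment.
4. In Step 3, state the sample size as a total that is consistent with the reconciled volumes and the October 2018 completion date.

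The cost is a rewritten paragraph, one recalculation and one added sentence. The stated figures will probably look less favourable, but no extra enrolment is required.
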